**Discussion:**

This study will assess whether simply asking people to reflect on the extent to which they may anticipate regret for not registering as an organ donor increases organ donor registration 6 months later. If successful, this simple and easy to administer theory-based intervention has the potential to save lives and money for the NHS by reducing the number of people receiving treatments such as dialysis. This intervention may also be incorporated into future organ donor campaigns.

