### Pilot studies

The aim of the present study is to determine whether simply asking people whether they would later regret not registering as an organ donor increases verified registration. In preparation, we have conducted 3 pilot studies [for full details, see 11,12]. We found that simply asking people whether they would later regret not registering as an organ donor increased their intentions to register [12, Study 2]. Moreover, we replicated this finding with a more representative sample of the adult Scottish general public [12, Study 3]. Although these findings are promising, people do not always act upon their intentions, the well recognised intention-behaviour gap. In a third pilot study we found that asking people whether they would later regret not registering as an organ donor increased self-reported organ donor registration [11]. This latter finding suggests that anticipated regret promotes organ donor registration. However, this research can be criticised for using self-reported measures of registration. The acid test is clearly whether this intervention leads to a significant increase in *verified *registrations on the UK NHS Blood and Transplant (NHSBT) posthumous Organ Donor Register. The aim of the present study is to test whether a large scale, simple anticipated regret intervention leads to a significant increase in NHSBT verified organ donor registrations.

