### Research questions

(a) Does a brief, theory-based anticipated regret intervention lead to a significant increase in organ donor registrations?

(b) If we do observe an anticipated regret effect, what is the mechanism, e.g. is it fully mediated via intentions and/or non-cognitive affective attitudes?

(c) What effect size is observed, to inform the power calculation for the next stage, a UK-wide translational study?

(d) What is the feasibility, response rate etc. to inform such a study?

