### Design and materials

We will utilise a between-groups, prospective randomised controlled design (i.e. participants will be randomly allocated into one arm of the study). In line with previous research [11,12,18,34], we will manipulate anticipated regret by altering the questions that the participants complete. Participants will be randomly allocated into one of four conditions: no questionnaire control (NQC), questionnaire control (QC), theory of planned behaviour (TPB) questionnaire, and anticipated regret (AR) questionnaire (for an overview, see Figure 1). The latter three conditions are similar to O'Carroll and colleagues [11].

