### Outcomes

Our primary outcome variable is verified organ donor registration within 6 months of our postal intervention. Crucially, NHSBT has agreed to collaborate with us and perform a secure and confidential search of their organ donor register 6 months following our brief postal intervention. This search will tell us whether or not the participant is a registered organ donor and, if applicable, when they registered. NHSBT will conduct this anonymised search for all participants who have not opted out of the study, regardless of whether or not they returned the questionnaire. This will allow us to determine whether there is any bias caused by people being more willing to complete the questionnaire in certain conditions.

Our second outcome is intentions to become an organ donor in the future. If our anticipated regret intervention is successful we will test whether the increase in registration is due to participants having greater intentions to register as an organ donor. This outcome will be measured in our questionnaires, using the indices described above.

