### Analyses

Our primary analysis will be a logistic regression predicting donor status (registered vs. not registered) to explore the proportion of respondents who have registered as organ donors 6 months later as a function of the 4 arms. In this analysis we will control for any potential between-arm differences in age, gender and socio-economic status, if these are related to the outcome. We will conduct this regression with all participants who have not opted out of the study, regardless of whether or not they returned the questionnaire. Participants may not comply with their random assignment. That is, in this case, for some reason not complete and return the questionnaire. We will use instrumental variables (IV) regression techniques to estimate the causal effect of the intervention in compliers [see [38,39]]. Here randomization acts as the instrumental variable, compliance status as the endogenous variable. This technique is a viable alternative to traditional intention to treat (ITT) analysis. ITT treats randomization as a treatment, when in actuality it is the intervention, not the randomization that is the source of any effect. By treating assignment as an instrumental variable and intervention compliance as an endogenous variable, IV regression techniques reduce the bias in standard ITT analyses, and provide as estimate of the causal effect of the intervention in compliers [38]. These analyses will be conducted in M*Plus*-6 [40] and Stata [41]. We will also record the time interval between the questionnaire being sent out and date of organ donor registration to test for temporal effects.

If our intervention is successful, we will test the processes through which it occurs. We will assess whether the anticipated regret intervention promotes organ donor registration by increasing people's intentions to register and decreasing their emotions and non-cognitive affective attitudes towards organ donation. Essentially, we will test whether intentions and emotions mediate the effect of our intervention on registration. Simple tests of mediation will be implemented in ZUMASTAT [42]. More detailed tests of multiple and joint mediation as well as moderated mediation will be conducted using M*Plus*.

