### Evaluation

The effectiveness of the simple anticipated regret intervention will be assessed using the instrumental variables logistic regression analyses outlined above. This will determine whether there is a significant difference in the proportion of registered organ donors in each arm 6 months following our intervention. If we find that there is greater proportion of participants registered as organ donors in the AR arm than the other three arms, we will conclude that a simple anticipated regret intervention increases organ donor registration. We will also assess the mechanisms behind this intervention. The mediation analyses outlined above will test whether any significant effects of our intervention are due to increases in people's intentions to register and decreases in their emotions and non-cognitive affective attitudes towards organ donation.

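### Returning the questionnaire is only a proxy for receiving the intervention, so the claim that the complier (IV) estimate reduces bias is unsupported and effectiveness should not rest on it

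*Protocol article*

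**What the plan says.** Under Analyses, the primary analysis is a logistic regression of registration on the four arms. It includes everyone who did not opt out, returners and non-returners alike. The same paragraph then introduces non-compliance, defined as participants who "for some reason not complete and return the questionnaire", and sets up the IV model: "Here randomization acts as the instrumental variable, compliance status as the endogenous variable". It presents this as an alternative to intention to treat that lowers bias and yields the causal effect in compliers, and attaches no condition to that statement.

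Under Evaluation, effectiveness "will be assessed using the instrumental variables logistic regression analyses outlined above". Research question (c) asks: "What effect size is observed, to inform the power calculation for the next stage, a UK-wide translational study". It does not say which estimate supplies the answer.

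The intervention itself is described in two ways. The abstract's Discussion speaks of "simply asking people to reflect on the extent to which they may anticipate regret for not registering as an organ donor", and Pilot studies gives the aim as testing whether "simply asking people whether they would later regret not registering as an organ donor increases verified registration". Design and materials says "we will manipulate anticipated regret by altering the questions that the participants complete". Posting the form back is nowhere given as part of the mechanism. According to Organ donor registration, all four arms receive a registration form and are told of online, telephone, post and text routes. According to Outcomes, the register is searched for everyone who has not opted out.

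**The concern.** Everyone allocated to the anticipated regret (AR) arm is mailed the regret items. Someone who reads and thinks about them, or fills them in and leaves them on the table, has been exposed to the question. The IV analysis codes that person as unexposed.

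The complier estimate divides the as-randomised difference by the proportion counted as compliers. It therefore attributes the whole difference to returners, which is correct only if allocation changes nothing in non-returners (the exclusion restriction). The protocol does not state that condition, and its own account of the intervention gives reason to doubt it.

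What is at stake is the size and meaning of the reported effect: the figure used to judge effectiveness, and possibly the figure carried into the power calculation for the UK-wide study.

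**Working it through.** **Inputs**
- Return rate *r*: 23% to 37% (Recruitment).
- Completed questionnaires needed per arm: 565. Number to distribute at 23% return: 2,460. Number mailed per arm after allowing for existing donors: 3,630 (all Recruitment).
- *s*, the share of non-returners who read the items, and *k*, their effect relative to that in returners. The protocol gives neither, so both are assumptions and are shown as ranges.

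**The plan's own figure.** 565 / 0.23 = 2,456.5, or 2,457, against 2,460 stated. This reproduces up to rounding. The same return rate becomes the denominator of the complier estimate.

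**Formula.** Work on the risk-difference scale with a comparator not exposed to the items. Let *d* be the true effect in returners.
- As-randomised difference = *d* × [*r* + *k*(1 − *r*)*s*]
- Complier (Wald) estimate = as-randomised difference / *r*
- Complier estimate / *d* = 1 + *k*(1 − *r*)*s* / *r*

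At 23% return this is 1 + *k*(0.77)*s*/0.23. For example, with *k* = 1 and *s* = 10% it is 1 + 0.077/0.23 = 1.33.

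| *s* | *k* | *r* = 23% | *r* = 37% |
|---|---|---|---|
| 0% | any | 1.00 | 1.00 |
| 10% | 1 | 1.33 | 1.17 |
| 25% | 1 | 1.84 | 1.43 |
| 25% | 0.5 | 1.42 | 1.21 |
| 50% | 1 | 2.67 | 1.85 |
| 100% | 1 | 4.35 | 2.70 |

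The last row is the extreme in which return carries no information about exposure. The factor is then 1/*r*.

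**Direction.** If the items put non-returning readers off, *k* is negative and the estimate is too small. With *k* = −0.5, *s* = 25% and *r* = 23%, the factor is 1 − 0.42 = 0.58.

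**Check by simulation.** Settings were 3,630 per arm, an assumed 5% base rate, an assumed 5-point effect in all who read, 23% return and *k* = 1, ignoring the later exclusion of existing donors. The mean complier estimate was 5.1, 9.2 and 13.4 points at *s* = 0, 25% and 50%. The formula gives 5.0, 9.2 and 13.4. The corresponding as-randomised differences were 1.2, 2.1 and 3.1 points.

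**Test under the null.** With no effect of the items, the as-randomised test rejected in 4.7% of simulated trials. Dividing by the return rate rescales the estimate and its standard error together, so the test is essentially unchanged.

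**The case against.** Five points can be made for the plan.

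1. *Completion is also part of the description.* A reader might infer that the protocol always treats being asked as the intervention and so contradicts itself. It does not. The abstract's Methods, Design and materials, and the AR questionnaire section all speak of participants completing items, and the Regret section describes rating regret as well as thinking about it. Defining compliance by completion is defensible. What remains is that completing and returning are different events, and the model uses return.

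2. *Inflation is not established.* A reader might infer that the complier effect is certain to be inflated, or is an upper bound. Neither follows. There is no inflation if non-returners are unaffected, and the bias reverses if the items deter readers. The Background itself warns that blatant regret questions can be taken as emotional appeals and weaken the intervention. The multipliers also rest on a risk-difference ratio, whereas Evaluation names an IV logistic model, and the article does not say how compliance is coded in the comparator arms. This objection stands, and the figures are illustrations only.

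3. *The enclosed registration form is not a separate fault.* A reader might think that people who use the form and skip the survey break the condition. All arms get the form, so these people matter only if the allocated items changed what they did.

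4. *The as-randomised regression is already primary.* This is true, and it does not have the problem. But Evaluation passes over it and names the IV analysis as the basis for effectiveness.

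5. *Harm to the next study is conjectural.* Research question (c) does not name an estimate, and question (d) collects the response rate. On the risk-difference scale, the complier effect times that rate returns the as-randomised difference. This is fair: an undersized study follows only if the complier figure is used alone.

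Sensitivity tables may also belong in a fuller plan, and the timetable leaves the analytic strategy to be finalised in months 7–12. That does not excuse an unconditional claim of bias reduction that is already in print.

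**Conclusion.** The point holds in a limited form. Return is a proxy for exposure, the complier estimate needs an effect of zero in non-returners, and the protocol gives no ground for that assumption. The statement that IV lowers bias compared with intention to treat is therefore unsupported as written, and Evaluation should not rest effectiveness on it.

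If non-returning readers respond in the hypothesised direction, the complier effect is overstated. The illustrative factor at 23% return runs from 1.00 (none affected) through 1.42 (*s* = 25%, *k* = 0.5) to 2.67 (*s* = 50%, *k* = 1), and the factors are smaller at 37% return. These figures assume a risk-difference scale, an unexposed comparator, and values of *s* and *k* that the plan does not provide.

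The documents do not support reading this as a threat to the trial's significance test, or as proof that the complier figure is too large.

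**What to change.** 1. In Analyses, delete the claim that IV reduces bias compared with intention to treat.
2. In Evaluation, make the as-randomised by-arm regression of all who did not opt out the basis for effectiveness.
3. For research question (c), name the as-randomised AR minus TPB difference among those analysed as the effect size carried forward.
4. Keep the complier estimate as a secondary result. State that return is a proxy for exposure, label the estimate as conditional on no effect in non-returners, and give a sensitivity range over *s* and *k* that includes negative *k*.

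No new data are needed, because register outcomes are already to be traced for returners and non-returners alike. The cost is some rewording, one extra table and a smaller headline effect than the complier figure.

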### Evaluation

The effectiveness of the simple anticipated regret intervention will be assessed using the instrumental variables logistic regression analyses outlined above. This will determine whether there is a significant difference in the proportion of registered organ donors in each arm 6 months following our intervention. If we find that there is greater proportion of participants registered as organ donors in the AR arm than the other three arms, we will conclude that a simple anticipated regret intervention increases organ donor registration. We will also assess the mechanisms behind this intervention. The mediation analyses outlined above will test whether any significant effects of our intervention are due to increases in people's intentions to register and decreases in their emotions and non-cognitive affective attitudes towards organ donation.

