## Background

There is an insufficient supply of donor organs to meet the demand for organ transplantations worldwide. Over 10,000 UK residents are currently on the waiting list for a solid organ transplant, and 3 patients die per day before they receive a transplant [1]. A recent survey found that 90% of the UK general public approve of organ donation [2]. Despite this, only 30% of people in the UK (38% in Scotland) have registered as posthumous organ donors. This discrepancy suggests that there are important barriers that deter people from registering as an organ donor. The UK Government has set aspirational targets for increasing numbers on the Organ Donor Register from the current level of 17 million to 25 million by 2013, and to increase the number of organs donated by 73% [2]. There is therefore an urgent need to identify factors that promote and overcome the barriers that deter people from registering as an organ donor [3].

Traditional social-cognitive models postulate that actions are determined by rational-cognitive factors. For example, the theory of planned behaviour (TPB) [4] suggests that actions are determined by rational cognitive attitudes, subjective norms and perceived control. According to this theoretical model, people are likely to register as posthumous organ donors when they have a positive attitude towards donation ('organ donation is a benefit to humanity'), think that significant others support registration ('my family and friends think that I should register as an organ donor'), and believe that they have the ability to register ('it is easy for me to register as an organ donor'). Indeed, most behaviour change interventions adopt such social cognitive approaches. Information is given that is designed to change people's thoughts and perceptions of a specific health behaviour. For example, in 2009 the Gift of Life campaign used the slogan "Be a hero, put the kettle on", which aimed to increase organ donation by emphasising that registration was quick and easy, thus trying to alter people's perceived control over this action. Moreover, this slogan also associated organ donation with positive perceptions ('being a hero'), thereby increasing people's positive attitude towards this action. According to the TPB, such campaigns are likely to be effective. However, without rigorous scientific evaluation, it is difficult to determine their effectiveness.

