## Method/design

### Recruitment

Participants will be a large, randomly selected representative sample of the adult Scottish general public. These participants will be randomly selected from a list containing 1.2 million members of the adult Scottish general public. Participants will be posted a brief questionnaire, together with information about, and a link to the UK Organ Donor Register. We will be receiving informed consent from all participants. However, we were concerned that if we were to require all participants to return signed consent forms by post, it is likely that people who are more likely to register as an organ donor would be more likely to participate in our study. This would create an unacceptable bias that could render our results scientifically meaningless. We are, therefore, using an 'opt-out' approach in which participants are required to contact us if they do not want to take part in the study. We will make it very clear that people do not have to participate if they do not wish to, and we have made it as easy as possible to withdraw either by; (a) ticking a form and returning it to us in the stamped addressed envelope that we provide to all, (b) email or (c) telephone. We believe that our approach is justified as; (a) no harm will come to the participants, (b) our research cannot be practically carried out if we had to receive written informed consent from all participants, (c) the potential benefits to the NHS (i.e. determining effective methods of increasing organ donor registrations) outweigh the cost, and (d) NHSBT will be conducting the search of the organ donor register, not us, we will never have access to individual identifiable results, and we will never know whether a specific individual has registered or not, only NHSBT will have this information, and crucially, they would have it regardless of whether this study was conducted or not.

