Based on our pilot data [11], we estimate that in order to identify a significant effect at the conventional .05 alpha level, at a power of .80, we would need 565 completed questionnaires per condition. As with any questionnaire based study there are likely to be many people who do not complete our survey. The response rate for this type of survey ranges from 23% to 37% [37]. Based on the conservative lower estimate (23%), we calculate that we would need to distribute 2,460 questionnaires per condition in order to gain a sufficient number of completed surveys. Furthermore, we also need to oversample to account for the proportion of the adult Scottish general public that are already registered donors. Adjusting for this, we need to distribute 3,630 surveys per condition in order to gain a sufficient number of completed surveys. Because there are four conditions in this study (for details, see below), we need to distribute a total of 14,520 questionnaires. The logistics of this national field based study will be conducted by Perspektiv, a market research company (http://perspektivred.co.uk). It should be noted that in the present study we improve on O'Carroll et al. [11] by including a no questionnaire control arm. We do not have pilot data that would allow us to conduct power calculations for this condition. However, based on the questionnaire control arm in O'Carroll and colleagues [11], we estimate that the above sample size estimates should be more than sufficient.

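### The Evaluation section rests effectiveness on an unspecified instrumental-variables logistic regression instead of the primary by-arm comparison, and common forms of that model do not recover the complier odds ratio

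*Protocol article*

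**What the plan says.** Two sections of the protocol article describe the main analysis.

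- **Analyses.** The primary analysis is a logistic regression of registration status on the four arms, in all participants who have not opted out, whether or not they returned the questionnaire. The section then adds IV regression, with the randomised arm as instrument and compliance (completing and returning the questionnaire) as endogenous variable. It justifies this by stating that "IV regression techniques reduce the bias in standard ITT analyses, and provide as estimate of the causal effect of the intervention in compliers". Mplus and Stata are named as software. No estimator is named.
- **Evaluation.** "The effectiveness of the simple anticipated regret intervention will be assessed using the instrumental variables logistic regression analyses outlined above". The section adds that this will show whether the proportion of registered donors differs in each arm. It would conclude that the intervention works if the proportion is greater in the anticipated regret arm than in the other three.

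Recruitment plans on the lower end of an expected response of 23% to 37%. Research question (c) says the observed effect size will inform the power calculation of a UK-wide study.

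**The concern.** There are two linked problems.

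**Which analysis decides.** Analyses makes the plain by-arm regression primary. Evaluation gives the judgement of effectiveness to the IV model, then describes its output as a comparison of proportions by arm. An IV model with return as the endogenous variable estimates an effect among people who would return the questionnaire. That is another quantity in another population.

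**Whether the named model delivers its stated target.** Linear IV divides the arm difference in proportions by the return rate. Under the usual assumptions this is the complier risk difference. The logit scale has no such property, because odds ratios do not average over returners and non-returners. With 63% to 77% expected not to return, the dilution is heavy, so the error can be large when the two groups differ in their untreated tendency to register.

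At stake are the clarity of the effectiveness conclusion and the effect size carried into the next trial. An odds ratio of 4 where the truth is 2 would leave that trial underpowered.

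**Working it through.** **The plan's own figure.** The only stated number built on the return rate is in Recruitment: "we calculate that we would need to distribute 2,460 questionnaires per condition". Check: 565 / 0.23 = 2,456.5, which agrees after rounding. The 23% is therefore the planning value for compliance. The protocol states no figure for the IV analysis itself.

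**Inputs.**
- Return rate π = 0.23, with 0.37 as the upper value (Recruitment).
- Assumed, because the protocol gives no registration rates: untreated risk pc0 in would-be returners, risk pn in non-returners, and a true complier odds ratio of 2.0, which fixes the treated complier risk pc1.
- Assumed structure: one questionnaire arm against the no-questionnaire arm, no access to the questionnaire in the latter, and no effect of a questionnaire that is not returned (exclusion restriction).

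**Formulas (large-sample limits).**
- Control-arm risk m0 = π·pc0 + (1 − π)·pn; questionnaire-arm risk m1 = π·pc1 + (1 − π)·pn.
- Predictor substitution: log OR = [logit m1 − logit m0] / π.
- Residual inclusion: log OR = logit pc1 − [logit m0 − (1 − π)·logit pn] / π.
- Linear IV (Wald): risk difference = (m1 − m0) / π.

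**Worked case: pc0 = 10%, pn = 3.5%, π = 0.23.**
- Odds 2 × 0.10/0.90 = 0.2222, so pc1 = 0.1818.
- m0 = 0.23 × 0.10 + 0.77 × 0.035 = 0.0500; m1 = 0.23 × 0.1818 + 0.77 × 0.035 = 0.0688.
- By-arm log OR = −2.6058 + 2.9455 = 0.3397 (OR 1.40).
- Predictor substitution: 0.3397 / 0.23 = 1.477, OR 4.38.
- Residual inclusion: −1.5041 − [−2.9455 + 0.77 × 3.3168] / 0.23 = −1.5041 + 1.7025 = 0.198, OR 1.22.
- Linear IV: (0.0688 − 0.0500) / 0.23 = 0.082, equal to the true 0.1818 − 0.10.

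**Results, true complier OR 2.0.**

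| Return | pc0 vs pn | Predictor substitution | Residual inclusion | Linear IV = true risk difference |
|---|---|---|---|---|
| 23% | 5% vs 5% | 2.39 | 2.00 | 0.045 |
| 23% | 6% vs 4% | 3.04 | 1.87 | 0.053 |
| 23% | 10% vs 3.5% | 4.38 | 1.22 | 0.082 |
| 23% | 15% vs 2% | 6.77 | 0.28 | 0.111 |
| 37% | 10% vs 3.5% | 3.34 | 1.39 | 0.082 |
| 37% | 15% vs 2% | 4.04 | 0.55 | 0.111 |

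**Under no effect (pc1 = pc0, 23% return).** Predictor substitution gives 1.00, because m1 = m0. Residual inclusion gives 0.61 at 10% vs 3.5% and 0.14 at 15% vs 2%. In simulations with 2,250 per arm (3,630 × 0.62, after removing the 38% already registered), residual inclusion rejected a true null in 12% and about 80% of trials respectively. Linear IV rejected in 4–5%.

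**Direction over a wider grid.** In 105 scenarios at each return rate (pn 1–8%, pc0 1–15%, true OR 1.25–2), predictor substitution never reversed the sign. Residual inclusion did so in 44 at 23% return and in 39 at 37%.

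**The case against.** The strongest reply is that the protocol does not propose either failing estimator. It never says two-stage, and it names Mplus, where a complier-class (principal-stratum) model with a logit link can be fitted. That model recovers the complier odds ratio under the exclusion restriction. The analytic strategy is also to be finalised in months 7–12, before the register check. This stands as far as it goes: a reader might infer that the protocol has fixed a wrong estimator, and the text does not support that. What remains is that one label covers methods giving 4.4, 1.2 or 2.0 on the same data, and effectiveness is to be assessed under that label.

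A reader might also infer that the planned analysis can get the sign wrong or reject a true null. That arises only with residual inclusion, and only when untreated risks differ. Predictor substitution on a single contrast without covariates keeps the by-arm sign and the null.

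The size depends on assumed risks. The largest figures need a 7.5-fold gap (15% vs 2%). Recruitment says "it is likely that people who are more likely to register as an organ donor would be more likely to participate in our study", but that concerns a requirement to return signed consent forms. It makes such a gap plausible; it neither predicts one among questionnaire returners nor gives its size.

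The formulas fit only contrasts with the no-questionnaire arm. The questionnaire control and planned-behaviour arms also receive questionnaires, so neither the error figures nor the complier-risk formula carries over to them.

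Finally, the by-arm regression is already planned as primary, and the conclusion rule is worded in proportions. This limits the harm to direction and significance. It does not settle which analysis decides, nor correct a wrong complier effect size.

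**Conclusion.** The concern holds in a limited form. Analyses and Evaluation disagree on which analysis judges effectiveness, and Evaluation treats a complier effect as a comparison of proportions by arm. That follows from the text alone.

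The estimator problem is conditional. If a common two-stage logit form were used at 23% return against the no-questionnaire arm, a true complier odds ratio of 2.0 would be reported as 2.4 to 6.8 (predictor substitution) or 2.0 down to 0.28 (residual inclusion), depending on how far returners and non-returners differ in untreated risk. With equal risks, residual inclusion is exact and predictor substitution is off by about a fifth. All of this assumes one-sided non-compliance and the exclusion restriction. Linear IV and principal-stratum estimates need the same assumptions, and reading the items without returning them would weaken all three.

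**What to change.** 1. In Evaluation, state that effectiveness is judged by the by-arm comparison in all participants who have not opted out, that is, the primary logistic regression of the Analyses section.
2. In Analyses and Evaluation, replace the IV logistic regression with a supportive complier analysis against the no-questionnaire arm: linear IV (two-stage least squares, equivalent to the Wald ratio) on the risk-difference scale with robust standard errors.
3. If an odds ratio is wanted, form it from two estimated complier risks with a bootstrap interval. The treated risk is the observed risk in returners of the questionnaire arm. The untreated risk is (control-arm risk − non-return share × non-returners' risk) / return share. A named principal-stratum model with a logit link would also serve.

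The cost is a few sentences, in software already named, with no new data. The downside is that the headline complier figure becomes a risk difference rather than a regression odds ratio. Against the no-questionnaire arm it describes the whole questionnaire; the added effect of the regret items still rests on the by-arm comparison with the planned-behaviour arm.
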